**Methods:**

This open-label, non-randomised clinical vaccine trial (ClinicalTrials.gov, NCT05332197, registered on 31 March 2022, URL:
https://clinicaltrials.gov/study/NCT05332197) will assess the safety and immunogenicity of a booster dose of the licensed 17D YF vaccine in Gambian children. The trial will recruit 750 children in three cohorts of different ages (250 each). All children were vaccinated with the 17D YF vaccine at 9–10 months of age as part of clinical trials run by the Medical Research Council (MRC) Unit The Gambia, and are thus well-characterised, including basic clinical, anthropometric, and post-primary immunogenicity data. The children will receive booster doses at 15 months, 4 years, or 8.5 years. Serum samples will be taken before and 28 days after the booster, with additional sampling for exploratory endpoints in subgroups. Adverse events are solicited for the first three days following vaccination and recorded throughout the study period. The primary objective of the trial is to describe the safety and immunogenicity of the booster in the different age cohorts. Secondary objectives are to characterise the rate of sero-reversion (change from seropositive to seronegative) over a period of 9 months to 8 years following single primary vaccination and to profile the immune response to the booster to explore underlying mechanisms for the longevity of vaccine-induced antibody.

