### Study objectives

The main objective of this trial is to assess if a yellow fever (YF) booster dose is required for children who received a single dose of YF vaccination in infancy and if so, at what age this booster dose might be most effective to administer.

Primary:

To describe the safety and immunogenicity of a booster dose of a licensed YF vaccine administered to three different age cohorts of children, following a documented primary dose of a yellow fever vaccine administered at nine months of age.

Secondary:

To characterise the rate of YF PRNT seroreversion (seropositive to seronegative) over a period of 9 months to 8 years following a single primary dose of yellow fever vaccine administered to Gambian infants at nine months of age.To profile the immune response to the booster dose of YF vaccine in order to explore underlying mechanisms for longevity of vaccine-induced antibody.

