**Figure 1. f1:**
[figure not shown]
Study design.

This trial will be conducted at one site: Fajikunda Health Centre in Fajara, The Gambia. Children previously enrolled in each of the three historic vaccine trials (summarised in
Table 1) will be recalled and invited for participation in the booster study. We will enrol until we have re-recruited 250 children per cohort. A roughly equal number of male and female participants will be enrolled in each cohort, but no absolute percentage figures will be set. Following individual sensitization and informed consent, basic clinical and anthropometric data will be collected, and children will have a pre-booster blood sample (5–10ml depending on age) taken for YF PRNT
_50_ (
Figure 1). All children will then receive a booster dose of a licensed 17D YF vaccine in use in The Gambia. All vaccines will be administered by the MRCG team. Local and systemic reactogenicity data will be solicited for 3 days. All children will then be invited back at day 28 (+/-7-day window) for a second blood sample (5–10 ml depending on age) and PBMC will be isolated and stored at the same timepoint (
Figure 1). If, based on initial laboratory work, it is determined that a smaller number of PBMC will be required at this timepoint, only serum will be collected for post-booster YF PRNT
_50_. A smaller cohort in each age group will be enrolled in the sub-study described below.

**
*Sub-studies*
**

In order to conduct systems biology investigations, which will provide novel insights into YF immune responses in children, subgroups of 30 children in each cohort will also be consented for a further sample (max. 5 ml) at either Day +7 for RNASeq or Day +14 for analysis of T cell responses (
Figure 1). The aim is to enrol the first 30 eligible children per cohort in the sub-studies, following consent provided on consent form version 1.0. Any child in these cohorts will have a maximum of 3 blood samples (up to 5 ml in the youngest age group, up to 10 ml/timepoint in the older age groups.)

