Solicited adverse events (AE) will be collected up to and including Day 3 following the booster vaccination. On Day 1, a member of the field team will conduct a home visit to assess and record any local or systemic AE including the presence of fever. Any child with a local or systemic response of concern will be reviewed by a study clinician the same day or within 24 hours according to the nature of the complaint. On Day 2 and 3 following vaccination, a member of the field team will contact the family by telephone to follow up on any ongoing or new local or systemic reaction. If there are any additional concerns, a home visit or clinic visit will be arranged as judged necessary by the study clinician. After Day 3 and until the end of the study, unsolicited adverse events will be collected. Parents will be asked to contact the study team to report any potential adverse events. These will be reviewed accordingly, and safety data recorded.

Immunology subgroups:

30 children per age cohort will be included in the immunology sub-studies which require a further blood sample on either Day 7 (+/-1) or Day 14 (+/-3) following the booster vaccination. For this purpose, the child will attend the clinic for blood sampling (see
Table 2).

**
*Final study visit*
**

On the final visit at Day 28 (+/-14), the child will be examined, and a further blood sample of 5–10 ml will be collected (5 ml for children under 5 years, up to 10 ml for older children).

**
*End of study*
**

The total duration of the clinical phase of the trial will be 12 months. This phase will end once up to 250 participants per age group have been enrolled and completed their D28 post booster vaccination visit. We will not substitute dropouts. The total duration of the trial is 18 months, and the trial will be considered as ended once the database has been cleaned and locked, the close out monitoring visit conducted and the end clinical study report submitted to MCA and to the IEC.

**
*Clinical evaluations*
**

During Visit 1 and Visit 2, clinical examination, vital signs, height and weight will be carried out and documented in the eCRF.

**
*Laboratory evaluations*
**

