Redness/Erythema ‡ (size as well as grade will be collected)	No redness/ erythema	≤ 2.5cm in diameter	> 2.5cm in diameter with < 50% of the surface area of the extremity segment involved (e.g. lower arm or thigh)	≥ 50% of the surface area of the extremity segment involved (e.g. lower arm or thigh) OR ulceration OR secondary infection OR phlebitis OR sterile abscess OR drainage	Potentially life- threatening consequences (e.g. abscess, exfoliative dermatitis, necrosis involving dermis or deeper tissues)
Swelling/induration ‡ (size as well as grade will be collected)	No swelling/ induration	≤ 2.5cm in diameter	> 2.5cm in diameter with < 50% of the surface area of the extremity segment involved (e.g. lower arm or thigh)	≥ 50% of the surface area of the extremity segment involved (e.g. lower arm or thigh) OR ulceration OR secondary infection OR phlebitis OR sterile abscess OR drainage	Potentially life- threatening consequences (e.g. abscess, exfoliative dermatitis, necrosis involving dermis or deeper tissues)

§ any AE resulting in death will be defined as grade 5 severity. ‡ grading based on the greatest single diameter or measured surface area. Based on the National Institute of Health, Division of AIDS (DAIDS) Table for Grading the Severity of Adult and Pediatric Adverse Events – Corrected Version 2.1 July 2017.

**Table 2B. T2B:** Systemic solicited adverse events.

Systemic	Grade 0	Grade 1 Mild	Grade 2 Moderate	Grade 3 Severe	Grade 4 § Potentially Life Threatening
Acute allergic reactions	No acute allergic reaction	Localized urticaria (wheals) with no intervention indicated	Localized urticaria (wheals) with intervention indicated OR mild angioedema with no intervention indicated	Generalized urticaria OR angioedema with intervention indicated OR symptoms of mild bronchospasm (wheeze)	Anaphylaxis OR life-threatening bronchospasm (wheeze) or laryngeal oedema (stridor)
Axillary Temperature	< 37.5°C	37.5 to 38.4°C	38.5 – 38.9°C	39.0 – 40.0°C	> 40°C
Vomiting	No vomiting	Transient or intermittent AND no or minimal interference with oral intake	Frequent episodes with no or mild dehydration – oral rehydration solution indicated	Persistent vomiting resulting in orthostatic hypotension OR aggressive rehydration indicated (e.g. intravenous fluids)	Life threatening consequences (e.g. hypotensive shock)

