Diarrhoea	No diarrhoea	Liquid stools (less formed than usual) but usual number of stools	Liquid stools with increased number of stools OR mild dehydration	Liquid stool with moderate dehydration	Life threatening consequences (e.g. liquid stool resulting in severe dehydration, hypotensive shock)
Irritability	No irritability	Crying more than normal/irritability but no or minimal interference with usual social and functional activities	Crying more than normal/irritability causing greater than minimal interference with usual social and functional activities	Crying more than normal/irritability preventing usual social and functional activities	Requiring hospitalization due to irritability
Drowsiness	No drowsiness	Sleeping more than normal/drowsiness but no or minimal interference with usual social and functional activities	Sleeping more than normal/drowsiness causing greater than minimal interference with usual social and functional activities	Sleeping more than normal/drowsiness preventing usual social and functional activities	Requiring hospitalization due to drowsiness
Appetite	Eating/ feeding normally	Eating/feeding less than normal but no or minimal interference with usual social and functional activities	Eating/feeding less than normal with greater than minimal interference with usual social and functional activities	Eating/feeding less than normal preventing usual social and functional activities	Requiring hospitalization due to not eating/feeding.
Rash at a site other than product administration site	No rash	Localized rash at a site other than the product administration site.	Diffuse rash OR target lesions	Diffuse rash AND vesicles or limited number of bullae or superficial ulceration of mucous membranes at one site	Extensive of generalized bullous lesions OR ulceration of mucous membranes involving two or more distinct mucosal sites OR Stevens-Johnson syndrome OR toxic epidermal necrolysis.

§ any AE resulting in death will be defined as grade 5 severity. Modified from the National Institute of Health, Division of AIDS Table for grading the severity of adult and pediatric AE – Version 2.1 July 2017; US Department of Health and Human Services, Food and Drug Administration, Guidance for Industry, Toxicity Grading Scale for Healthy Adult and Adolescent Volunteers Enrolled in Preventative Vaccine Clinical Trials, Sep 2007.

**
*Serious adverse events (SAEs)*
**

An AE will be considered to be serious (i.e. SAE) if:

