The risks to either infants, pre-school children or school age children taking part to this study are low, as the YF vaccines used in this trial are licensed, have proven to be safe, and these children have initially received a YF vaccine in previous trials and via routine EPI programs worldwide without raising major safety concerns. Also, the vaccines are currently used in the routine EPI schedule in The Gambia and as such trial participation per se is not associated with any increase in risk with this regard.

Nonetheless, the administration of any vaccine can be associated with local and systemic adverse reactions which can be severe or, exceptionally rarely, even life-threatening. The safety of participants will be monitored closely for 30 minutes following vaccination as standard practice by the investigator, local safety monitor and sponsor.

Blood sampling can cause some pain at the time and occasionally results in the development of a bruise but has no other risks. The volumes of blood to be taken, even in infants, are not of physiological significance.

Receiving a booster vaccine for Yellow Fever could be of significant benefit for these children living in an endemic setting for the disease and who, outside of this trial, are unlikely to receive this booster.

**
*Informed consent*
**

For those expressing an interest for their children’s participation, informed consent will not be undertaken on the same day as individual sensitization to ensure all caregivers have the chance to consider the information overnight, at least, prior to providing consent.

Written/thumb-printed informed consent will only be required from one caregiver, but in all cases, it will be confirmed that other caregivers are aware of the study and are supportive.

For children who are 6 years of age and above, oral assent will be obtained from them in addition to their caregiver’s written/thumb-printed consent. This oral assent will be documented in the clinical notes.

Information regarding the trial will initially be given to caregivers by a field worker or nurse, although all caregivers will also be given the chance to ask a study clinician any questions they may have regarding the trial prior to the assessment of understanding and consent documentation.

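### Table 2B has one systemic solicited list for all ages and no named item or grade for symptoms an older child feels, so these are absent from the older cohorts' solicited reactogenicity summary

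*Protocol article*

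**What the plan says.** The Abstract gives the ages: "The children will receive booster doses at 15 months, 4 years, or 8.5 years". The primary objective (Study objectives) is "To describe the safety and immunogenicity of a booster dose of a licensed YF vaccine administered to three different age cohorts of children". Under Study design, all children are followed in the same way: "Local and systemic reactogenicity data will be solicited for 3 days".

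Safety considerations ties active surveillance up to Day 3 to Tables 2A (local) and 2B ("Systemic solicited adverse events"). Table 2B is not split by age. Its eight rows are acute allergic reaction, axillary temperature, vomiting, diarrhoea, irritability, drowsiness, appetite and rash. Grade 1 irritability, for example, reads "Crying more than normal/irritability but no or minimal interference with usual social and functional activities".

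Other routes exist. Under Follow-up, "On Day 1, a member of the field team will conduct a home visit to assess and record any local or systemic AE". The telephone calls on Days 2 and 3 also ask about new reactions, and Table 2 marks unsolicited event collection from Visit 1. Data presentation and analysis names solicited and unsolicited events as separate items to summarise.

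**The concern.** In a 15-month-old, crying, sleeping and feeding are reasonable proxies for feeling unwell. A child of 8 may instead say that the head or the legs hurt, and Table 2B has no row for that. The protocol accepts that its oldest cohort can answer for itself: "For children who are 6 years of age and above, oral assent will be obtained from them".

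The description of reactogenicity is therefore less complete in the older children than in the youngest. The trial's main objective asks at what age a booster might best be given, so readers may well set solicited systemic rates side by side by cohort. A lower rate in older children could then partly reflect what was asked.

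**Working it through.** The plan states no figure on this point, so the check is mainly a reading of the tables.

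**Step 1: sort the eight rows of Table 2B.**
- Applicable at any age (5): allergic reaction, temperature, vomiting, diarrhoea, rash.
- Behaviour observed by a caregiver (3): irritability graded by crying, drowsiness by sleeping, appetite by eating or feeding.
- Subjective systemic symptoms as felt by the child: 0.

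The only symptom a child can self-report by name is injection-site pain, which is in the local table (2A).

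**Step 2: follow an unlisted symptom, such as headache on Day 2 in an 8-year-old.** It is not prompted by name. The telephone call may bring it out, because the call asks openly about new reactions. Table 2 allows unsolicited collection from Visit 1, while the Follow-up text describes that collection as starting after Day 3, so the route in the first three days is not clearly fixed. If recorded, the symptom has no grading row in 2A or 2B. It is an unsolicited event and adds nothing to the solicited summary.

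**Step 3: which cohorts.** Self-report is supported only for the 8.5-year cohort (assent from age 6), which is 250 of 750 children. The 4-year cohort, another 250, is affected in part, through what caregivers can relay.

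**Step 4: illustration of size.** Neither input below is in the documents. Let p be the true Day 0-3 incidence of an unlisted symptom and c the share captured by open or unsolicited reporting. With n = 250:

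- expected = 250 × p
- unrecorded = 250 × p × (1 − c)
- unrecorded in percentage points = 100 × p × (1 − c)

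| p (assumed) | Expected | Unrecorded, c = 70% to 30% | Points |
|---|---|---|---|
| 5% | 12.5 | 3.75 to 8.75 | 1.5 to 3.5 |
| 10% | 25 | 7.5 to 17.5 | 3 to 7 |
| 20% | 50 | 15 to 35 | 6 to 14 |

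At c = 50% the three rows give 6.25, 12.5 and 25 children, or 2.5, 5 and 10 points. In the solicited summary the count for the symptom is zero whatever c is.

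**Step 5: overlap.** For a child-level measure of any systemic reaction, a child with headache and fever already counts through the fever row. If a share s of affected children also has a listed event, the loss falls to 250 × p × (1 − c) × (1 − s). The figures in Step 4 are therefore upper limits for that measure.

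**Step 6: scale.** Table 3 gives precision for seroconversion, not safety, but a 95% interval for any proportion at n = 250 has the same width. The Wilson interval at 90% reproduces the plan's 85.7 to 93.1. Its mirror image at 10% is 6.9 to 14.3, a half-width of (14.3 − 6.9) / 2 = 3.7 points. A loss of 5 points (p = 10%, c = 50%, s = 0) would exceed that half-width. A loss of 1.5 points (p = 5%, c = 70%, s = 0) would not.

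**The case against.** The strongest reply is that nothing here is misstated and that one common list is a defensible choice, because it makes the cohorts comparable on the same items. The following parts stand.

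- The safety objective is descriptive. Differences between cohorts are planned only for immunogenicity, and no composite of any solicited systemic reaction is defined. A reader might infer that the plan builds in a biased comparison favouring a later booster. The documents do not support that, because they contain no such comparison. On the eight shared items, a reading across cohorts would be the same after the fix.
- A reader might call the whole list infant signs. Five of the eight rows fit any age. The other three are graded against interference with ordinary activities, which can apply to older children, and drowsiness partly overlaps tiredness.
- A reader might say that such symptoms go unasked or ungraded. Open enquiry covers Days 1 to 3, and the documents do not say that unsolicited events are left ungraded. The record forms are not shown. What can be said is that the symptoms are not prompted by name and have no row in either solicited table.

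The reply does not remove the gap in description. Open enquiry is not the same as a named prompt, and an event recorded as unsolicited does not appear in the solicited summary. What is asked at the visit is set by the protocol, so a later analysis plan cannot fully recover it.

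**Conclusion.** The point holds in a limited form. That unlisted subjective symptoms are absent from the solicited summary follows directly from Table 2B and from the separate summaries of solicited and unsolicited events. Under-capture across all adverse events in the older children is probable in direction, but its size cannot be derived from the documents.

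The range of 2.5 to 10 points at half capture rests wholly on assumed incidence and capture. It is an upper limit for any child-level measure of systemic reaction, so it should not be cited as an estimate of bias. Nor should the full 500 older children be treated as able to self-report, since the protocol supports that only for the 250 in the 8.5-year cohort.

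The practical consequence arises only if solicited systemic rates are read across age cohorts. This is a low-cost improvement to the safety description and leaves the immunogenicity endpoint untouched.

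**What to change.** For any further use of this form, add headache, muscle or joint pain, and tiredness or malaise for the 8.5-year cohort, and for the 4-year cohort through the caregiver where feasible. Grade them on the functional scale already used in Table 2B. Keep the eight common items as the only basis for reading across cohorts, and report the added items separately by cohort.

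The Discussion and conclusion states that recruitment and follow-up are complete, so new prompts cannot help this trial. Here, tabulate unlisted systemic symptoms with onset on Days 0 to 3 by cohort, from the open-enquiry and unsolicited records. State in the report that solicited systemic rates in the older children omit subjective symptoms.

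The cost for reuse is about three rows on the reactogenicity form and eCRF, asked at contacts already scheduled. The drawback is a slightly longer form and added items that cannot be compared with the 15-month cohort. For this trial the cost is one extra table and a sentence on the limitation.

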### Statistical considerations

**
*Sample size considerations*
**

The primary endpoint of this study is the PRNT titres post booster vaccination according to intervals between primary YF vaccination and the booster dose. A sample size of 250 participants per cohort provides a precision of around +/- 5% over a range of plausible seroconversion rates associated with boosting at the three different timepoints (
Table 3).

**Table 3. T3:** Precision around given estimates of seroconversion based on a sample size of 250 participants per group.

Seroconversion	95% confidence interval
95%	91.6 – 97.1
90%	85.7 – 93.1
80%	74.6 – 84.5
70%	64.1 – 75.3
60%	53.8 – 65.9
50%	43.9 – 56.2

The same sample size also provides over 80% power to detect a 10% difference in the seroconversion/seroreversion rates between two cohorts assuming a rate of at least 85% in one cohort, and over 90% power to detect a 15% difference in any two seroconversion/seroreversion rates.

Exploratory immunology sub-studies:

Our previous systems biology studies showed that significant differences in “omic” signatures over the first week of life and according to day of life were detectable in cohorts of infants as small as n=10 per group. We cannot currently confirm if such “omic” changes are informative to predict responses to YF vaccine in young children, but based on the data from Querec
*et al.*, systems biology approaches were informative in adults in group sizes as small as n=15
^
25
^. We are therefore confident that a group size of 30 per sub-group will provide us with sufficient datasets to not only explore if “omic” signatures in children are also predictive of humoral responses to the booster, but also to interrogate pathways and cellular populations involved in mediating correlates of protection against yellow fever.

**
*Data presentation and analysis*
**

Baseline data:

All baseline data including demographic and anthropological parameters will be tabulated by age cohort along with appropriate measures of spread. 

Immunogenicity data:

Descriptive evaluations including yellow fever PRNT GMT, seropositivity, seroreversion rates between 9 months and boost and seroconversion rates following boost (including the number of participants who seroconvert or who have a four-fold rise in antibodies concentrations) and relevant differences in these measures between age cohorts will be calculated and presented with appropriate measures of spread.

GMT data will be log
_2_ transformed for analyses. Two-sided 95% confidence intervals (CI) for the log transformed means will be estimated assuming a Student’s t-distribution. These will be converted to the original scale by calculating 2
^L ^: 2
^U^, where L and U are the limits of the 95% CI of the log-transformed means.

GMT ratios and their 95% CIs will be calculated in the same manner. The log
_2_ ratio is the mean difference of the log
_2_ transformed data with a two-sided 95% CI estimated via a two-sample t-test and the interval is reverse transformed as above to obtain the 95% CI on the original scale. If, after log transformation, the normality assumption is not tenable, 95% CIs will be estimated using bootstrapping. Titre distributions by age cohort pre-boost and post-boost will be illustrated using reverse cumulative distribution (RCD) plots.

Safety data:

Summary statistics including appropriate measures of spread will be calculated for all safety data including solicited local and systemic AEs and unsolicited AEs. Safety events including AEs and SAEs will additionally be provided.

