## Introduction

### Background

Yellow fever (YF) virus is a mosquito-borne flavivirus found in Sub-Saharan Africa and tropical South America. The virus causes YF, a viral haemorrhagic fever, which can be prevented by a highly effective live-attenuated vaccine, however, it is now considered a re-emerging disease due to the increased numbers of cases in the last 30 years
^
1
^. Across Africa, 13 countries in West, Central and East Africa reported yellow fever cases in 2023 and 2024, with a case fatality rate of 11%
^
2
^. The median age of these cases was 25 years, with over two thirds of cases (69%) over the age of 15 years, suggesting a potential contribution of waning immunity to increased disease susceptibility
^
2
^.

In most endemic countries across sub-Saharan Africa and South America, the YF vaccine is administered alongside other Expanded Programme on Immunization (EPI) vaccines, including the first measles containing vaccine (MCV1), at nine to 12 months of age. Several recent publications from Africa and Brazil have raised doubts that a single dose of YF vaccine provides sufficiently long-lasting immunity. In a cohort of children vaccinated at around nine months of age in Ghana, seropositivity, measured by microneutralization assay, had fallen from an already low 73% at 28 days following primary vaccination to 28% at 2.3 years
^
3
^. This figure had increased to 43% by six years, perhaps as a result of natural exposure or unrecorded re-vaccination. Our own data from samples collected in The Gambia and Mali 6 years post primary YF vaccination administered via the routine EPI program showed that 22.2% of a cohort of 467 children had undetectable antibody concentrations, with another 7.5% revealing concentrations below the threshold of seropositivity of 0.5 IU/mL, confirming a substantial long-term decline in immunity
^
4
^. Cross-sectional studies in Brazil, including nine-month to 12-year olds, have similarly described a progressive decrease in the seropositivity rates from 87% within the first six-months after vaccination to 42% at six to eight years
^
5
^. A recent systematic review summarised the findings of 36 studies on over 17,000 participants aged 6 months to 85 years from 20 countries across the world, including Sub-Saharan Africa
^
6
^. In children vaccinated under the age of 2 years, the pooled seroprotection rate in a meta-analysis using a random effects model was 52% at 5 years following primary vaccination
^
6

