### Selection and withdrawal of participants

**
*Selection of participants*
**

The study will recruit 750 healthy children to receive the booster dose of YF vaccine. A roughly equal number of boys and girls will be recruited. We do not expect there to be differences in the results by sex.

Participants will be recruited/ re-approached from the previously enrolled participants in each of the vaccine trials listed in
Table 1 below.

**Table 1. T1:** Cohorts to be re-approached as part of the trial.

Dates of 9-month yellow fever vaccination	Age in January 2022	Number of infants	Co-administered vaccines in original study	Serology in primary study	Study reference
Jul 2013 – May 2014	8 years 6 years	~1504	Combinations of IPV and measles and rubella	PRNT _50_	NCT01847872 SCC1327
Feb 2018 – Aug 2018	4 years	~675	Measles and rubella, OPV and PCV	PRNT _50_	NCT03197376 SCC1517
Dec 2020 – May 2022	9 months	~320	Measles and rubella, OPV and PCV	PRNT _50_	NCT03606096 SCC1600

Upon screening, potentially eligible children will continue until the end of study unless the trial is stopped for some reason. A child may be excluded from the trial for the purposes of vaccination and/or clinical sampling or if ongoing participation is considered to be against their best interests or if a contraindication to vaccination and/or to the obtaining of clinical samples is identified. Such decisions will be made by the PI in discussion with other members of the clinical trial team and/or the sponsor. A child excluded in this way would be replaced and hence this would not alter the target sample size of 750. If not enough children from the previous cohorts are available, we will aim to recruit appropriate age groups from community health centres. We expect this to be an exception rather than the rule.

**
*Eligibility of participants*
**

Participants must meet all of the inclusion criteria and none of the exclusion criteria to be eligible to participate in the trial. A representative sample of children will be recruited from the target population.

Inclusion criteria:

Any child fitting the required age cohorts who has a documented record of having received a primary dose of the Institut Pasteur YF 17D vaccine between 9 and 12 months of age. Documented evidence can be either a previous record of YF vaccination with dates in our own trial registers if the child was a previous participant or has documented evidence on its Infant Welfare Card.

Exclusion criteria:

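### The stated power for seroreversion counts all 250 children per cohort, although only those seropositive after priming can serorevert, and the 80% figure has no reserve for this or for unreplaced dropout

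*Protocol article*

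**What the plan says.** All of the following is in the protocol article.

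- **Statistical considerations, Sample size considerations.** "A sample size of 250 participants per cohort provides a precision of around +/- 5% over a range of plausible seroconversion rates". Table 3 then gives 95% intervals for seroconversion rates from 95% down to 50%. The next paragraph makes two power claims. The first is: "The same sample size also provides over 80% power to detect a 10% difference in the seroconversion/seroreversion rates between two cohorts assuming a rate". Its condition is that one of the two rates reaches 85% or more. The second, with no such condition, is for larger differences: "over 90% power to detect a 15% difference in any two seroconversion/seroreversion rates". One cohort size serves both measures, and nothing is allowed for loss.
- **Study objectives and Study endpoints.** Seroreversion is the secondary endpoint. Both sections define it as the passage from seropositive to seronegative after the single primary dose.
- **Data presentation and analysis, Immunogenicity data.** The post-booster seroconversion summary includes children who seroconvert or who show a four-fold rise.
- **Selection of participants.** If the earlier trials yield too few children, "we will aim to recruit appropriate age groups from community health centres". This is expected to be exceptional. Children excluded by the investigator are replaced.
- **End of study.** "We will not substitute dropouts". The same paragraph ends the clinical phase once up to 250 per age group have enrolled and completed the day-28 visit.
- **Background.** Cited figures are 73% seropositive at 28 days after priming in Ghana and, in The Gambia and Mali six years after priming, "22.2% of a cohort of 467 children had undetectable antibody concentrations, with another 7.5% revealing concentrations below the threshold of seropositivity".

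**The concern.** The two rates are treated as if they shared one denominator. A seroreversion rate needs children who were seropositive after the primary dose. Primary non-responders are not at risk. A child recruited from a community health centre was not in the earlier trials, so no post-primary serum from them exists for that child. The usable number is therefore below 250 unless every child is a former trial participant who responded to priming.

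For seroconversion the issue is different. It concerns loss between booster and day 28, and which definition Table 3 has in mind.

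This section is the only numerical justification of the trial's size in the article, and the Discussion expects the results to inform WHO recommendations. A reader who sees no clear difference in seroreversion between cohorts would set it against a claimed power above 80% or 90% that the at-risk group may not provide.

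**Working it through.** **Inputs.** n = 250 per cohort, and the two power claims, are from Sample size considerations. The significance level is not stated for the power claims. I assume two-sided 5%, in line with the two-sided 95% intervals in the analysis section.

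**Formula.** Pooled z-test, equal groups, no continuity correction:

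power = Φ{ [ |p1 − p2| − 1.96 √(2p̄(1 − p̄)/n) ] / √([p1(1 − p1) + p2(1 − p2)]/n) }, where p̄ is the mean of the two rates.

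**Reproducing the plan's figures at n = 250.**

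- 85% against 75%, the hardest case under the 85% condition: [0.10 − 1.96 × √(2 × 0.80 × 0.20/250)] / √((0.1275 + 0.1875)/250) = (0.10 − 0.0701)/0.0355 = 0.842, so power is 80.0% (0.80003). The mirror case, seroreversion of 15% against 25%, gives the same value.
- 57.5% against 42.5%, the hardest 15-point case: (0.15 − 0.0877)/0.0442 = 1.410, so power is 92.1%.
- Table 3 matches Wilson intervals at n = 250 in every row, except that the lower limit at 50% comes out at 43.8 against the printed 43.9.

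The full cohort was therefore the denominator throughout.

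**Power at smaller evaluable numbers.**

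| n per cohort | How it arises | 85% v 75% | 57.5% v 42.5% |
|---|---|---|---|
| 250 | plan | 80.0% | 92.1% |
| 249 | one child fewer | 79.8% | 92.0% |
| 238 | 95% seropositive after priming (assumed), or 5% loss (assumed) | 78.0% | 90.8% |
| 225 | 10% loss (assumed) | 75.7% | 89.2% |
| 213 | 15% loss (assumed) | 73.4% | 87.5% |
| 182 | 73% seropositive after priming (Ghana figure in Background) | 66.6% | 81.9% |

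The 10-point claim falls below 80% from n = 249 down. The 15-point claim falls below 90% from n = 231 down, so it needs at least 232/250 = 92.8% of each cohort evaluable.

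**Which rows apply to which measure.** Seroreversion compares the post-primary with the pre-booster sample, so its shortfall comes from post-primary status (238 to 182), and day-28 dropout does not touch it. Seroconversion combined with four-fold rise uses every child with paired samples, so only dropout matters (238 to 213).

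**Precision.** With modest loss the Wilson half-width hardly moves: at an 80% rate it is 4.9 points at n = 250, 5.2 at 225 and 5.4 at 213. It changes materially only if Table 3 means strict seroconversion among children seronegative before the booster. The cited 22.2% + 7.5% = 29.7% gives 0.297 × 250 ≈ 74 children. The half-width is then 7.0 points at 90% and 11.1 points at 50%, against 3.7 and 6.2 at n = 250.

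**The case against.** **There is no miscalculation.** This stands: both power statements are true at n = 250. The fault lies in the denominator.

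**A reader might infer that seroconversion, like seroreversion, applies only to a subset.** The article does not support that. Its analysis section brings four-fold rise into the seroconversion summary, so a child already seropositive before the booster can respond. The result for about 74 children holds only under the strict definition, which Table 3 neither adopts nor rules out.

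**The precision statement is fair.** It says around 5 points, and Table 3 prints the wider limits at lower rates. I do not count this against the plan.

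**The boundary case is the hardest one.** This also stands. At 90% against 80%, power is 88.2% at n = 250 and still 82.6% at 213, though 76.4% at 182. A reader might also point to differences around a 30% rate, where power is lower even at 250. Those lie outside the condition attached to the 10-point claim and do not contradict it.

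**Dropout may not arise.** Ending at up to 250 completers could be read as a target of 250 completers. That sits awkwardly with not substituting dropouts, so the text is ambiguous and does not prove a shortfall. No dropout rate is given.

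**The inputs are borrowed and the analysis is descriptive.** The Ghana figure is from another cohort and assay, community recruits are meant to be exceptional, the primary endpoint is titres, and reported intervals will show the precision achieved. This limits the consequence, but a power claim that includes seroreversion still needs the right denominator.

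**Conclusion.** The point holds for seroreversion: its power is stated on all 250 children per cohort, while its definition admits only those documented seropositive after priming. Over 73% to 95% seropositive (182 to 238 children), power is 67% to 78% for the boundary 10-point difference, against a claim above 80%, and 82% to 91% for the hardest 15-point difference, against a claim above 90%. The lower end is illustrative and the upper end is an assumption.

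For the seroconversion composite the point is smaller and depends on loss: 78% to 73% and 91% to 87% at an assumed 5% to 15%, with precision almost unchanged. Precision fails clearly only if Table 3 refers to strict seroconversion, which the article leaves open. The documents do not show that all the stated precision and power are undelivered.

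**What to change.** In Sample size considerations:

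1. State the denominator of each measure: children seropositive after priming for seroreversion, and children with paired samples at day 28 for the composite of seroconversion and four-fold rise.
2. Recompute seroreversion power on the expected number seropositive after priming. The Rationale says that post-primary results are already documented for most children, so the trial's own counts can replace the 73% to 95% range used here. Say how children without a post-primary result are handled.
3. Restate the composite's power on expected day-28 completers, with the loss assumption shown as a range. Figures such as 76% and 89% at 10% loss illustrate one assumption and should not be entered as fact.
4. Say which definition of seroconversion Table 3 uses. If it is the strict one, recompute the table on the expected number seronegative before the booster.
5. In End of study, reconcile the rule on dropouts with ending at up to 250 completers.

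The cost is wording and a short recalculation. No further children are needed, and recruitment and follow-up are in any case complete. The stated figures become less favourable.
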